## Abstract

**Background:**

Accurate shade matching in dentistry is crucial for achieving aesthetic outcomes, with increasing patient expectations driving advancements in shade selection technologies. Color perception is influenced by multiple factors such as incident light, reflection, absorption, observer variability, and environmental conditions. The evolution of shade-matching tools now includes digital and artificial intelligence (Al)-assisted appliances aimed at improving accuracy and ease of use.

**Objective:**

This study aims to compare and evaluate the efficacy of AI-assisted appliances, namely, smartphone cameras, digital single-lens reflex (DSLR) cameras, and intraoral scanners in selecting tooth shades in clinical practice.

**Results:**

This study was intramurally funded in December 2024. Data collection is scheduled to commence following the publication of this study protocol. As of submission, no participants have been recruited, and data analysis is yet to begin. Results are expected to be completed and published in early January 2026.

**Conclusions:**

This study aims to establish a standard protocol for the use of Al-assisted, easily accessible tools such as smartphones and DSLRs for dental shade selection. These devices, being user-friendly and nontechnical, could democratize the process of shade matching, benefiting both clinicians and patients by improving restoration outcomes while reducing costs and complexity. Our results will contribute to the growing body of digital dentistry literature and support the integration of practical Al tools in everyday clinical practice.

**Trial Registration:**

Clinical Trials Registry-India CTRI/2024/07/070002; https://tinyurl.com/4pt5eutb

**International Registered Report Identifier (IRRID):**

PRR1-10.2196/68160

## Introduction

Aesthetic dentistry has seen a vast demand to meet the requirements of the patients to achieve a perfect smile and is playing a vital role in contemporary dentistry. To ultimately meet the aesthetic requirements, dental restorations must precisely mimic the shade of the teeth [1]. The instruments used for shade matching are constantly evolving in dentistry due to the growing demand from patients for more aesthetic results. Numerous factors can affect the intricate process of color perception, including incident light, light reflection, light absorption, the observer's visual matching, and the object's surroundings [2].

Shade selection is broadly classified into 2 methods, namely, subjective and objective methods. Subjective methods rely on traditional tools such as the conventional Vita Shade Guide System and Vita Classic Shade Guide, while objective methods use advanced instruments, often powered by artificial intelligence (AI), including spectrophotometers, colorimeters, and intraoral scanners [3]. The accuracy of the subjective approaches used to choose shades for the vita shade guide and vita classical shade guide is influenced by the chromatic perception disability. Numerous factors such as the environment of the clinics and the reflection of light contribute to subjective techniques [4].

AI-based systems minimize human error in tooth shade selection, which is often affected by subjective factors such as lighting conditions, visual fatigue, and individual perception [5]. AI algorithms analyze digital images of teeth in real time, ensuring a more consistent and accurate shade selection by comparing them to vast databases of tooth shades. AI technology can be integrated with intraoral scanners, spectrophotometers, and colorimeters to automatically identify and suggest the most accurate shade. AI refines measurements by eliminating inconsistencies, compensating for lighting variations, and ensuring that the most accurate shade is selected based on the collected data [3].

A spectrophotometer is considered the gold standard for this purpose [6]. The spectrophotometer utilizes a 6500K light source to accurately match tooth color and displays the results by using a visual shade guide. Despite certain drawbacks such as the need for costly, nonintuitive, and technique-sensitive equipment, spectrophotometry remains a versatile and highly efficient method for shade matching [6]. However, given its limitations such as cost and limited accessibility in small dental practices, portable alternatives such as colorimeters were introduced to provide a more practical option for shade matching [6].

A colorimeter, which measures an object's spectrum reflectance or transmittance to determine its color attributes, is an alternative for choosing digital shades [7]. They usually use precise light sources and sensors to measure tooth color accurately. To determine how much light is reflected or transmitted onto the tooth, the colorimeter emits light onto it. Utilizing this measurement, the gadget provides numerical values in a given color space, like CIELAB coordinates [8]. However, this technique's drawback is that it may not be as exact at reproducing hues, especially for teeth with complex tones or translucency. Additionally, environmental factors such as illumination can affect colorimeter readings, requiring exact calibration and standardization [8].

Recent advancements in dentistry have led to an increase in the use of intraoral scanners, some of which can produce vivid images and distinguish between soft and hard tissues. Shade color information from intraoral scanners is also based on the visual shade criteria [9]. Additionally, scanners are able to identify tooth color and distinguish between the architecture of teeth and the oral cavity. The cost of the technology is one of the most significant challenges, and only some smaller or wealthier clinics may be able to afford it. The use of digital single-lens reflex (DSLR) and smartphone pictures as AI tools for choosing tooth shades is becoming more popular in modern dentistry as a solution to these problems because of their capacity to integrate sophisticated AI-driven analysis with excellent image capturing. Finding the ideal shade for dental restorations is made easier, more accessible, and more precise by these technologies. DSLR cameras provide high resolution and excellent image quality, making it possible to see the tooth's surface, texture, and translucency in great detail. AI software can subsequently process these photos to more precisely determine the shade. The number of dentists using their smartphones for photography is rapidly increasing due to the complex operation and manipulation of DSLR cameras [10].

However, the accuracy of evaluating the tooth shade by using smartphone cameras may vary based on a number of factors such as lighting and camera quality. The dentist can enhance the image for better shade-matching results by adjusting the camera angle or lighting conditions based on real-time feedback from AI algorithms on smartphones. Nonetheless, it remains a feasible and reachable substitute [11]. In this study, we will compare the efficacy of DSLR and smartphone cameras against that of intraoral scanners for selecting tooth shades. In order to accomplish this, factors such as color accuracy, image quality, and clinical user-friendliness will be assessed. This kind of comparison could help to determine the most effective method for accurately determining the tooth shade in dentistry. Posterior teeth will be included in this study, as they will be included as additional variables to assess the potential differences in shade selection accuracy across tooth types. This may influence the outcomes due to variations in morphology, translucency, and light reflection. Thus, the objective of this study is to evaluate the scope of readily accessible AI-assisted appliances for determining dental shades in aesthetic dentistry.

## Methods

### Study Design and Participants

This will be an observational study conducted in the Department of Prosthodontics and Crown & Bridge at Sharad Pawar Dental College and Hospital, Sawangi, Wardha, Maharashtra, India. The inclusion criteria and exclusion criteria are shown in Textbox 1. To reduce observer bias, the individuals responsible for analyzing and comparing the shade-matching outcomes (based on laboratory values) will be blinded to the device used for capturing the tooth shade (smartphone, DSLR, or intraoral scanner). Each image or scan will be coded and deidentified prior to analysis, ensuring that the evaluators are unaware of the imaging modality. All data will be stored securely and entered into a centralized, password-protected database. Double data entry will be employed for cross-verification, and all files will be time-stamped and logged for traceability.

Inclusion and exclusion criteria for this study.

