### Data Collection Procedure

A total of 221 participants will be recruited from the outpatient department. To choose their shade, study participants will be exposed to an intraoral scanner, a smartphone, and a DSLR. The study participants will be informed about the study and asked to sign a consent form prior to the procedure. The participants will be instructed to clean their teeth and take off any makeup before the test. The treatment will be performed on the patients' maxillary central incisors by using 3 different technologies: an intraoral scanner, a DSLR, and a smartphone camera.

Shade selection using a smartphone (iPhone 12; software version iOS 12.5.2.) will be performed using natural daylight or daylight-mimicking LED lights that are ideal for accurate color reproduction. The smartphone camera will be positioned parallel to the patient's face at a distance of 30 cm and zoomed in to focus on the teeth of interest, that is, the maxillary central incisors. Photos will be then imported into the Adobe Photoshop software to obtain the L*a*b values.

Photographic color selection will be done using the DSLR camera (Canon EOS 200D) with a macro lens for close-up shots with high detail and resolution. The DSLR camera will be set to manual mode to grant full control over exposure, aperture, and white balance settings, allowing for optimal customization to capture high-quality images for shade selection. The tooth would be placed at a distance of about 22-28 centimeters from the DSLR camera. The L*a*b values will then be acquired by importing the photographs into the Adobe Photoshop software.

For color selection, the Cerec Primescan (Dentsply Sirona) intraoral scanner will be used. The vita classic color selection mode will be activated in the scanner's software. We will scan the maxillary central incisor and note the color that is detected. The L*a*b values will be determined.

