### Statistical Analysis

R software (version 4.3; R Foundation for Statistical Computing) will be used to calculate all the results. Descriptive statistics (mean, standard deviation) will be calculated for tooth shade measurements obtained from each method. Intermethod agreement will be evaluated using Bland-Altman plots or intraclass correlation coefficients. Subgroup analyses will be conducted to explore potential factors influencing intermethod agreement (eg, tooth condition, presence of restorations). Sensitivity and specificity analyses will be performed to evaluate the accuracy of smartphone and DSLR cameras compared to that of intraoral scanners by using the latter as the reference standard. Statistical significance will be set at *P*<.05. Additionally, a paired 2-sided *t* test or Wilcoxon signed-rank test will be used to compare the mean shade differences between each pair of methods (intraoral scanner vs smartphone camera, intraoral scanner vs DSLR camera, smartphone camera vs DSLR camera). The effectiveness of a smartphone and DSLR camera in various dental procedures such as examining the existence of restorations or enamel anomalies will be assessed in a subgroup analysis. In this study, we will test statistical assumptions (eg, normality, homoscedasticity) and apply multiple testing corrections (eg, Bonferroni or false discovery rate) to ensure valid inferences. The intraoral scanner will serve as the reference standard for sensitivity and specificity analyses, using ΔE ≤ 2.0 as the threshold for clinically acceptable shade matches.

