## Discussion

A smartphone, DSLR camera, and intraoral scanner will be used to capture and match the shade of a patient's teeth. The smartphone offers a simple portable tool for basic shade reference, while the DSLR camera provides high-quality, controlled images for accurate shade matching under standardized lighting. The intraoral scanner creates a detailed 3D map of the teeth, enabling precise, customized shade selection that can be compared with physical shade guides for optimal restoration outcomes. Advancements in digital dentistry, such as colorimeters, intraoral scanners, and computer-aided shade matching systems, have significantly transformed the shade selection process [13]. These technologies have greatly improved treatment outcomes and patient satisfaction by offering greater accuracy, efficacy, and consistency in shade matching. This study focuses on evaluating the efficiency of smartphone cameras and DSLR cameras in the field of tooth shade selection. Our research seeks to determine their utility as alternatives to subjective methods and cost-intensive objective method for shade selection in dentistry. A study conducted by Yung et al [14] compared the color consistency of digital images captured in a clinical setting by using smartphone cameras and single-lens reflex (SLR) cameras. They found that color accuracy is not considerably increased by using a polarizer. An effective substitute would be a smartphone camera that has an external light source attached to it.

Ziadeh et al [15] assessed the repeatability of the intraoral scanner for selecting dental shades in the anterior and posterior regions. They found that the intraoral scanner demonstrated better repeatability in the anterior region when compared to the visual method, and the difference between the two approaches is clinically acceptable. Faezeh et al [12] examined the validity of color selection techniques by using visual assessments, intraoral scanning, and photography (using an SLR camera and a smartphone). By evaluating and contrasting the dependability of the 3 most popular methods of color selection, that is, visual assessment, intraoral scanning, and photography, oral scanners showed more accurate results.

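### Coding the files cannot keep evaluators from knowing whether a record came from the scanner or a camera, so the blinding claim should be narrowed and the Photoshop reading protected

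*Protocol article*

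**What the plan says.** Under Study Design and Participants, the Protocol article sets out its safeguard against observer bias in two steps. It first names who is masked: "the individuals responsible for analyzing and comparing the shade-matching outcomes (based on laboratory values) will be blinded to the device". It then gives the means and its effect: "Each image or scan will be coded and deidentified prior to analysis, ensuring that the evaluators are unaware of the imaging modality". Coding and de-identification are the only means described.

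Data Collection Procedure describes what each device produces:
- **Smartphone** (30 cm, zoomed): "Photos will be then imported into the Adobe Photoshop software to obtain the L*a*b values".
- **DSLR** (macro lens, about 22-28 cm): "The L*a*b values will then be acquired by importing the photographs into the Adobe Photoshop software".
- **Intraoral scanner:** "The vita classic color selection mode will be activated in the scanner's software", followed by "We will scan the maxillary central incisor and note the color that is detected". The L*a*b values are then to be determined, by a route the article does not describe.

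The Discussion adds that "The intraoral scanner creates a detailed 3D map of the teeth". Statistical Analysis gives the scanner a different role from the cameras: "The intraoral scanner will serve as the reference standard for sensitivity and specificity analyses, using ΔE ≤ 2.0 as the threshold".

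**The concern.** The article does more than plan to code the files: it asserts that coding guarantees a result. That result depends on the three outputs looking alike once labels are removed, and the article describes outputs that are not alike. The gap falls between scanner and camera, which is the comparison named as the primary outcome under Expected Outcome.

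Two things are at stake. First, a report that repeats the sentence would claim more masking than the described procedure can ensure. Second, the place where a person's judgement could enter is the reading of L*a*b values from photographs. The article does not clearly place that step inside the masking, and it does not say whether the reader can see the scanner result or the other camera's values for the same participant.

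**Working it through.** The point rests on no sample-size, power or error-rate figure. The check is a comparison of what is claimed with what is described.

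**1. What the mechanism does.** Coding and de-identification remove names and labels. No section describes a step that brings the outputs to a common appearance, such as cropping or export to one format.

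**2. Scanner versus camera.** The scanner record is a 3D scan accompanied by a shade that its own software detects. The camera records are flat photographs. These differ in kind, so a code on the file cannot hide which is which from someone who opens it. The scanner must also be identified at the sensitivity and specificity step, because it is the reference there.

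**3. Smartphone versus DSLR.** Both are photographs of the same incisors, imported into the same software. Distance, lens and lighting differ, so recognition is plausible, but no section says that it is possible. This part remains open.

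**4. Who is masked, and on what material.** The masked persons are those who analyse and compare outcomes, described as working from laboratory values. If these are L*a*b numbers, a table of them can be coded, and masking between the two cameras is achievable. The next sentence, however, speaks of images and scans. The Introduction also lists image quality among the factors to be assessed, which would normally require viewing the images. The article does not settle which material the evaluators see.

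**5. The exposed step.** The scanner shade is detected by software, so observer judgement there is limited. The camera values come from opening photographs in Photoshop, and no automatic extraction is described. The article does not say who does this or whether that person is among those masked. Assuming one reading per camera for each of 221 participants:

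221 × 2 = 442 camera readings pass through this step.

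This counts exposed readings. It does not estimate how many are biased.

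**6. How a reading could affect the result.** The match threshold is ΔE ≤ 2.0. Assume the ordinary L*a*b distance, ΔE = √(ΔL² + Δa² + Δb²); the article does not name a formula. Take a shift of 2 units in L* from the choice of sampling point, as an illustration only:
- Perfect match before the shift: √(2² + 0² + 0²) = 2.0, which still meets the threshold.
- Existing difference of 1 unit in L*, shift in the same direction: √(3² + 0² + 0²) = 3.0, no longer a match.
- Existing difference of 1 unit in L*, shift in the opposite direction: √(1² + 0² + 0²) = 1.0, still a match.

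Whether a pair changes class depends on the difference already present and on the direction of the shift. The documents give neither the spread of lightness across an incisor nor the distribution of ΔE, so the number of pairs affected cannot be computed.

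**The case against.** The strongest reply is that the article masks people who compare values, and numbers can be coded. No section says that these people open photographs or take the Photoshop readings. A reader given a coded, de-identified photograph is also not thereby told which scanner shade belongs to it. Operational details such as reading order are commonly left to a full protocol.

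Much of this stands. A reader might infer that all three devices can be recognised on sight and that the safeguard therefore does not exist. The article does not support that: recognition of smartphone versus DSLR is inference, and analysts of coded values can be masked between the cameras. A reader might also infer that the scanner shade is already known when the photographs are read. The article states no device order, describes the scanner last, and does not say where or by whom the shade is written down.

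The reply does not rescue the sentence itself. The sentence concerns images and scans and asserts a guarantee. For scanner versus camera, coding cannot give that guarantee to anyone who views the material. This is a positive statement in the article, not a detail left to another document.

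**Conclusion.** The claim that coding ensures unawareness of the device is an overclaim. It fails for scanner versus camera whenever the material itself is viewed, and that is the primary contrast. It can be made true for analysts who see only coded L*a*b values, as regards which camera is which. The manual reading that produces the camera values is not clearly protected.

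The direction of any bias cannot be stated. It is tempting to say that it would favour the expected result, but the article expects two things: the Abstract anticipates that the cameras can match the scanner, and the end of the Discussion anticipates higher reliability for the scanner. These pull in different directions. The size is also unknown. The 442 readings rest on one reading per camera per participant, and the ΔE illustration rests on an assumed formula and an assumed shift.

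The wording should be corrected and the reading step protected. The article reports no recruitment as of submission, so on that status both changes can precede data collection.

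**What to change.** 1. Delete the closing clause of the coding sentence, the part that asserts unawareness of the device. Limit the masking claim to analysts of coded L*a*b values, who do not know which camera is which. State that the scanner is identified to them as the reference. Full masking of all three devices is not available for the sensitivity and specificity analysis.
2. State who takes the Photoshop readings and from what material. Have that reader work from coded photographs in random order, using a sampling area fixed before any photograph is read.
3. Withhold the participant's scanner shade and the other camera's values from that reader until the readings are locked.

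The cost is a change of protocol wording and a small file-handling burden, chiefly holding back the scanner shade until the camera readings are locked. No extra visits or participants are needed.

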**Inclusion criteria**
Co-operative patients who are not anxious and are not apprehensiveAnterior maxillary central incisors will be usedPatients willing to participate in the study
**Exclusion criteria**
Teeth with any abrasionTeeth with enamel anomaliesAdjacent teeth with crown prosthesisTeeth with calculus and stains (extrinsic and intrinsic)Root canal–treated teethTeeth with restorationsFractured tooth (vertical and horizontal)

### Data Collection Procedure

A total of 221 participants will be recruited from the outpatient department. To choose their shade, study participants will be exposed to an intraoral scanner, a smartphone, and a DSLR. The study participants will be informed about the study and asked to sign a consent form prior to the procedure. The participants will be instructed to clean their teeth and take off any makeup before the test. The treatment will be performed on the patients' maxillary central incisors by using 3 different technologies: an intraoral scanner, a DSLR, and a smartphone camera.

Shade selection using a smartphone (iPhone 12; software version iOS 12.5.2.) will be performed using natural daylight or daylight-mimicking LED lights that are ideal for accurate color reproduction. The smartphone camera will be positioned parallel to the patient's face at a distance of 30 cm and zoomed in to focus on the teeth of interest, that is, the maxillary central incisors. Photos will be then imported into the Adobe Photoshop software to obtain the L*a*b values.

Photographic color selection will be done using the DSLR camera (Canon EOS 200D) with a macro lens for close-up shots with high detail and resolution. The DSLR camera will be set to manual mode to grant full control over exposure, aperture, and white balance settings, allowing for optimal customization to capture high-quality images for shade selection. The tooth would be placed at a distance of about 22-28 centimeters from the DSLR camera. The L*a*b values will then be acquired by importing the photographs into the Adobe Photoshop software.

For color selection, the Cerec Primescan (Dentsply Sirona) intraoral scanner will be used. The vita classic color selection mode will be activated in the scanner's software. We will scan the maxillary central incisor and note the color that is detected. The L*a*b values will be determined.

